# TRANscranial direct current stimulation for FOcal Refractory epilepsy in mitochondrial disease (TRANSFORM): delayed-start, randomised, double-blinded, placebo-controlled study

**DOI:** 10.1186/s12883-024-03907-6

**Published:** 2024-10-22

**Keywords:** Mitochondrial disease, Mitochondrial epilepsy, Pharmacoresistant epilepsy, Delayed-start study design, Refractory focal seizures, Transcranial direct current stimulation (tDCS), DC stimulation, Cathodal neuromodulation

## Abstract

**Background:**

Focal epilepsy is common in children and adults with mitochondrial disease. Seizures are often refractory to pharmacological treatment and, in this patient group, frequently evolve to refractory focal *status epilepticus* (also known as *epilepsia partialis continua*). Where this occurs, the long-term prognosis is poor. Transcranial DC stimulation (tDCS) is a promising, non-invasive, adjunctive treatment alternative to common surgical procedures. Limited recruitment of study participants with this rare disease and the ethical challenges of administering a treatment to one group and not another, while maintaining strict methodological rigour can pose challenges to the design of a clinical study.

**Method:**

We designed the first delayed start, double-blinded, sham-controlled study to evaluate the efficacy of tDCS as an adjunctive treatment for focal epilepsy. We will include participants with a genetically confirmed diagnosis of mitochondrial disease with drug-resistant focal epilepsy aged ≥ 2 years, aiming to collect 30 episodes of focal *status epilepticus*, each treated for a maximum period of 14 days. The early start intervention arm will receive tDCS from day 1. The delayed start intervention arm will receive sham stimulation until crossover on day 3. Our primary endpoint is a greater than 50% reduction from baseline (on day 0) in seizure frequency assessed by 3x daily reporting, accelerometery, and video monitoring. Changes in the underlying epileptogenic focus within the brain related to the tDCS intervention will be assessed by magnetic resonance imaging (MRI) and/or electroencephalography (EEG).

**Discussion:**

Study results in favour of treatment efficacy would support development of tDCS into a mainstream treatment option for focal epileptic seizures related to mitochondrial disease.

**Trials registration:**

ISRCTN: 18,241,112; registered on 16/11/2021.

## Background

### Study rationale

The estimated prevalence of mitochondrial disorders is greater than 1 in 4300 [1, 2] and epileptic seizures are reported in about 20–60% of individuals with the diseas*e* [3–10]. Seizures are often refractory to treatment with antiepileptic drugs and neuronal dysfunction resulting from the underlying mitochondrial disease is thought to play a significant role not only in initiating but maintaining high levels of seizure activity. Diagnosis is guided by the clinical presentation, including lactic acidosis, refractory seizures, myoclonic seizures, neurodevelopmental delay or regression, stroke-like episodes or multiorgan dysfunction [11]. The prognosis for refractory seizure disorders due to mitochondrial disease is extremely poor and frequently associated with neurodegeneration [12, 13]. Whether increasing seizure activity contributes to neurodegeneration or is simply a consequence thereof is unclear. If the former, to improve quality of life and prognosis, new therapeutic approaches for suppressing seizure activity should be a priority.

Transcranial direct current stimulation (tDCS) non-invasively modulates cortical excitability through weak direct currents (typically 2 mA) applied through the scalp. In contrast to other electrical stimulation procedures, tDCS is significantly less invasive. Vagus nerve stimulation and deep brain stimulation typically involve invasive surgery, which carries risks including side effects of general anaesthesia, brain haemorrhage, infection, and accidental damage to other brain areas during device-implantation. In the long term, tDCS is potentially more cost-effective than taking multiple AEDs and inpatient (intensive care unit) treatment. Some AEDs require regular blood monitoring, which necessitates frequent hospital appointments. Intensive care admission and surgical procedures involve prolonged inpatient hospital admission. Hospital visits, both expected and unexpected, escalate costs (financial and non-financial) on caregivers (parents, siblings, partners, and families), even more so for children of school age.

Cathodal tDCS is thought to reduce the probability of sodium and calcium channel opening and thus the probability of action potential generation and seizure propagation. In addition, via a process of Long-Term Depression (LTD), a change in synaptic strength can be initiated that ultimately leads to structural long-term changes within the neuronal network [14, 15]. Several studies have provided evidence for the efficacy of tDCS in reducing the frequency of clinical seizures in people with refractory focal epilepsy [16–20]. Direct current stimulation may therefore control seizures by diverse mechanisms from reducing neural connectivity within epileptic networks and thus the probability of seizure propagation outside the epileptogenic zone, to reducing the energetic demands on mitochondria by indirect effects on spiking activity and possibly by direct effects on glia [21] and intracellular bioenergetics [22–24]; tDCS is thus a promising non-invasive, adjunctive treatment option for refractory epilepsy.

### Aims, objectives, and outcomes

This study aims to evaluate whether tDCS can serve as an effective adjunctive treatment to reduce focal epilepsy in people with mitochondrial disease. Reducing the number of seizures is a primary goal of treatment, making it a highly relevant outcome for both clinicians and patients. Seizure reduction is a commonly used and well-accepted metric in epilepsy research which can be objectively measured and is responsive to treatment, making it suitable for assessing the efficacy of tDCS. Sham stimulation will be used as a comparator to determine the true efficacy of the tDCS treatment by providing a baseline against which the effects of the active treatment can be measured.

As the *primary goal* we will assess the efficacy of tDCS, as an adjunctive treatment, in reducing the number of focal epileptic seizures experienced by children and adults with genetically confirmed mitochondrial disease.

The *primary endpoint* is a greater than 50% reduction in seizure frequency (number and duration of seizures, jerks/ min) from baseline (on day 0), based on the European Medicines Agency guideline of 26 July 2018 CHMP/EWP/566/98 Rev. 3 [25]. This will be assessed through daily reporting from specialists, nurses, research staff, relatives, and carers by means of a seizure diary, while accelerometery and video monitoring will corroborate seizure counts.

*Secondary objectives* will be fourfold:

We will assess seizure freedom (i.e., resolution of the focal epileptic event) after tDCS.Magnetic resonance imaging (MRI) and electroencephalography (EEG) will be used to determine whether tDCS treatment results in clinically evident changes in the epileptogenic focus.Finally, we will evaluate tDCS as a mainstream treatment option for focal epileptic seizures related to mitochondrial disease.

*Secondary endpoints* include:

Seizure freedom assessed by 3x daily seizure diary, accelerometery, video monitoring, and an end-of study EEG.discontinuation of the study due to adverse events;assessment of side effects by seizure diary;and clinically significant improvement in neurophysiology and/or neuroradiology findings against expected natural history.

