## Intervention procedures

### Randomization and intervention protocol

At baseline, participants will be randomly assigned to receive either sham stimulation (delayed-start group) or active tDCS (early-start group). The placebo group will receive double-blinded sham procedure for 2 days. On Day 3, all participants will receive the active tDCS intervention as an adjunctive treatment for up to day 14. The allocated intervention will not be modified.

At baseline, participants will be randomly assigned to one of two arms for each focal event:

In the **Early Start Group** participants will receive 20 min of active tDCS daily from the start of the intervention period (day 1) for up to 14 days. By default, each active stimulation treatment session starts with an automated ramp up of current to 2 mA over 15 s to keep participants blind to the intervention. For the early start group tDCS then continues for 20 min until it ramps down.

In the **Delayed Start Group** participants will receive sham-stimulation/placebo treatment on day 1 and day 2 of the intervention followed by up to 12 additional days of active tDCS (1x daily for 20 min). Like active tDCS, sham tDCS starts with an automated ramp up of current (from 0 to 2 mA over 15 s) to mimic the sensations observed with active tDCS and to keep participants blind to the intervention. For the sham tDCS the current stops after the 15s ramp up. This sham stimulation protocol is well supported by current literature [16, 17].

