
Pre-study EEGs and brain MRIs will be acquired as part of the participants’ standard care for diagnosis and localisation of the epileptic focus. MRI and EEG safety screening questionnaires will have been completed before each exam as part of participants’ standard care. In the absence of an MRI lesion, the tDCS target will be determined based on standard clinical scalp EEG. These procedures will not be part of the study, but neuroimaging results will be considered for treatment-related decisions (e.g., specification of the tDCS target) and treatment evaluation. Only the ‘end of study’ standard clinical EEG will be collected as part of the study. Participants will receive a post-intervention MRI procedure if considered necessary from a clinical perspective as part of the patients’ routine care. Those MRI scans are not a standard research assessment related to this study but will be included in the data analysis when consent has been explicitly obtained for that purpose.

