### Withdrawal and relevant concomitant care permitted during the study

Standard care for participants continues throughout the study. No intervention is prohibited. Participants have the right to withdraw from the study at any time without having to give a reason. The investigator may withdraw a participant from the study at any time if the investigator considers it necessary. As per consent, if participants are withdrawn from the study, the information already obtained will be kept. Patients will be able to continue their regular treatment. If they wish, patients will be able to continue their (daily) tDCS treatment according to the study treatment plan, even if they withdraw from the study. In that case, no further study data will be collected after withdrawal.

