### Post-intervention

Following the tDCS treatment period, participants will undergo the following assessment:

End of study EEG (obtained the day after the last intervention day).Further follow up through regular clinical care. For six months data will be collected from the patient’s medical record.

Unless the study is prematurely discontinued, the end of the study will be the date of the last visit of the last participant and/or the completion of all follow-up monitoring.

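### The EEG/MRI endpoint is compared with an expected natural history at a time when no sham group remains, so it cannot show that tDCS changed the epileptogenic focus

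*Protocol article*

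**What the plan says.** Under Aims, objectives, and outcomes, the protocol article says that MRI and EEG "will be used to determine whether tDCS treatment results in clinically evident changes in the epileptogenic focus". The matching secondary endpoint is "clinically significant improvement in neurophysiology and/or neuroradiology findings against expected natural history". The Method paragraph of the Abstract repeats the causal wording: "Changes in the underlying epileptogenic focus within the brain related to the tDCS intervention will be assessed". The same Aims section also gives sham stimulation the job of separating the true effect of tDCS from everything else.

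The timing and conditions of the recordings are set elsewhere in the article:

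- **Crossover** (Randomization and intervention protocol): "On Day 3, all participants will receive the active tDCS intervention as an adjunctive treatment for up to day 14".
- **First recording** (Intervention administration and assessment procedures): "Pre-study EEGs and brain MRIs will be acquired as part of the" participants' standard care. It is not a study assessment.
- **Second recording** (Post-intervention): "End of study EEG (obtained the day after the last intervention day". It is scheduled once.
- **Repeat MRI** (Intervention administration and assessment procedures): "Participants will receive a post-intervention MRI procedure if considered necessary from a clinical perspective".
- **Stopping rule** (same section): tDCS ends when the event resolves or after 14 days, whichever comes first.
- **Co-treatment** (Withdrawal and relevant concomitant care permitted during the study): "Standard care for participants continues throughout the study. No intervention is prohibited".

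**The concern.** The objective asks a causal question about tDCS. The endpoint answers it by setting each event against a course that patients are expected to follow. An external benchmark of that kind has none of the protection that randomisation gives. Whatever else happens between the two recordings, such as a new anti-seizure drug, a dose increase or spontaneous recovery, moves the result in the same way as a tDCS effect would.

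What is at stake is a secondary conclusion. The Discussion says that favourable results would help make tDCS a mainstream option for this group, and the Aims section lists evaluating it as such among the objectives. A statement that tDCS changed the focus would feed that case without a control behind it.

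**Working it through.** The plan states no figure for this endpoint. Its only sample size belongs to the primary endpoint. It reproduces from the stated inputs: 10% against 30% at two-sided 5% and 90% power needs 82 observations per arm; the design effect is 1 + (14 − 1) × 0.10 = 2.3; 82 × 2.3 / 14 = 13.47, so 14 events per arm and 28 in total. That result has no bearing on the point here, which is about attribution.

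**Step 1. What differs between the arms at the end-of-study EEG.** The inputs are one session a day, sham on days 1 and 2 in the delayed-start arm, active treatment for all from day 3, and stopping at resolution or day 14. For an event whose last session is on day k, the early-start arm has had k active sessions and the delayed-start arm max(k − 2, 0).

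| Last session | Early start | Delayed start | Difference |
|---|---|---|---|
| Day 1 | 1 | 0 | 1 |
| Day 2 | 2 | 0 | 2 |
| Day 3 | 3 | 1 | 2 |
| Day 14 | 14 | 12 | 2 |

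From day 3 onward no event is on sham alone. The difference is at most two sessions for events of the same length. Its relative size depends on length: the delayed arm has 12/14 = 86% of the early arm's active exposure over the full course, but 1/3 = 33% for an event ending on day 3. Delayed-start events that resolve on day 1 or 2 never receive active tDCS, but they are identified by having resolved and so cannot serve as a control group.

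**Step 2. What can change the EEG between the two recordings.** The first recording comes from routine care before the study and the second follows the last session. Between them lie up to 14 days of treatment plus the interval before day 0. In that time tDCS is given, any other treatment may be started or increased, and the event may remit unaided. Improvement beyond expectation is the sum of these. The endpoint contains no term or comparison that isolates tDCS.

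**Step 3. When and in whom the second recording is made.** The EEG date depends on the outcome, because treatment stops at resolution and the EEG follows a day later. MRI is repeated only in events where clinicians want it, so the scanned events are a selected subset.

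**Step 4. What a comparison by arm would offer.** With 15 events per arm and a recording for each, the approximate 95% half-width for a difference in proportions is 1.96 × √(2p(1 − p)/15). The proportion improving is not in the documents. If it is assumed to be 10%, 30% or 50% in both arms, the half-width is 21, 33 or 36 percentage points. The comparison is randomised, but it is imprecise and contrasts early with delayed start.

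**The case against.** The best reply is that the endpoint may be only a way of judging each event: a clinician decides whether the EEG or MRI improved more than expected, and the arms are then compared. The Aims section does name sham as the trial's comparator, and Statistical analyses assigns other outcomes to mixed models or generalised estimating equations, which could include arm. A randomised comparison would balance drug changes on average. The meaning of natural history, and whether it is a treated course, could properly be set out in a full protocol or analysis plan that is not shown.

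Part of this stands. The article states no rule that every improvement counts as a tDCS effect, and the lack of a definition is not the complaint. But the comparator it does name is external, and no later detail can restore a sham group at the time of the EEG. Even on the generous reading, the arm comparison answers a question about early versus delayed start, not the one in the objective.

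Four stronger readings are tempting, and the documents do not support them:

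- **That every participant has had active tDCS by the end-of-study EEG.** The stopping rule makes this untrue for delayed-start events resolving on day 1 or 2.
- **That added drugs inflate the apparent success rate by some number of points.** No rate of added treatment is given and it could be zero. Entry requires drug-resistant epilepsy, which makes a response to an added drug less likely, though not impossible.
- **That unrestricted co-treatment undermines the primary endpoint.** For an adjunct, counting response whatever drugs are added is a legitimate choice, and a blinded sham arm runs alongside on days 1 and 2.
- **That drug changes go unrecorded.** The diary entry is optional, but medical records are source data and consent covers access to them until six months after study end.

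**Conclusion.** The point holds as one of attribution. As written, the EEG/MRI endpoint cannot support a conclusion that tDCS changed the epileptogenic focus, because improvement beyond an external expectation mixes tDCS with co-treatment and spontaneous recovery. This follows from the comparator, the EEG timing and the open co-treatment that the article itself fixes. It does not depend on how often drugs are added.

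The size of any bias cannot be estimated from the documents. What can be stated is the limit of the contrast: two active sessions at most between arms for events ending on the same day. The consequence is confined to a secondary endpoint. It calls for a change to what the trial says it will conclude, not to how it treats patients.

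**What to change.** Leave permitted care, the assessment schedule and the primary analysis as they are. In Aims, objectives, and outcomes:

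- **Objective.** Replace the wording that EEG and MRI "will be used to determine whether tDCS treatment results in clinically evident changes in the epileptogenic focus" with a statement that they will *describe* changes at the focus. Align the Abstract's Method paragraph.
- **Endpoint.** Replace "clinically significant improvement in neurophysiology and/or neuroradiology findings against expected natural history" with: *change in EEG, and in MRI where repeated, from the pre-study recording to end of study, reported by randomised arm.*
- **Interpretation.** Add: *a difference between arms reflects early versus delayed start of tDCS (at most two extra active sessions for events of the same length), not tDCS versus sham.*
- **Context.** List alongside each event the anti-seizure treatment changes between the two recordings, taken from the medical record.

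The cost is a few lines of wording and one listing from records the study already holds. No added procedure is needed. The real price is that the trial gives up a causal efficacy claim from the end-of-study EEG and MRI, which the design could not have supported.

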## Methods/ design

### Study design and participant management

This study follows a delayed-start, randomised, double-blind, sham-controlled design.

### Study setting

This single-site study will take place within the Wellcome Centre for Mitochondrial Research at Newcastle University, in collaboration with the NHS Highly Specialised Service for Rare Mitochondrial Disorders. All study assessments will be conducted in an adult or paediatric neurology ward at a tertiary care centre. Treatment sessions will be delivered on Newcastle-upon-Tyne Hospitals premises, unless the participant’s situation requires otherwise.

### Eligibility criteria

Adult and paediatric patients aged ≥ 2 years with a genetically confirmed diagnosis of mitochondrial disease and drug-resistant focal epilepsy as well as anatomically relevant changes related to focal seizures defined by neuroimaging and/or scalp EEG will be considered for inclusion. Drug-resistant focal epilepsy is defined by the International League Against Epilepsy (ILAE) as failure of two antiepileptic drugs to achieve sustained seizure freedom. Participants need to be able to undergo all study assessments and investigations in the opinion of the recruiting investigator in agreement with the participant/parents/legal guardian.

Participants will be excluded if they are aged < 2 years, have metallic or electronic implants, or have undergone other neurosurgical intervention (e.g. craniotomy) that typically preclude MRI scanning and/or tDCS treatment. People with other co-existing epileptic comorbidities e.g., brain tumour, traumatic brain injury, cortical dysplasia, or any other known uncontrolled medical problems that, in the opinion of the investigator, would preclude participation in the study will be excluded as well.

### Recruitment

This study will involve the assessment of at least 30 episodes of focal *status epilepticus* in participants with a genetically confirmed diagnosis of mitochondrial disease. This will either equate to the recruitment of 30 inpatient participants each presenting with one episode of focal *status epilepticus*, or fewer than 30 participants with individual participants contributing more than one episode of focal *status epilepticus* (provided each event per participant has a different focal location). If participants participate multiple times, they will be re-consented for each new focal event. If participants recruited into the study were already to be inpatients due to an acute episode of focal *status epilepticus* that cannot be resolved with antiepileptic drugs they will remain as such for the duration of their participation.

We host the largest UK mitochondrial disease patient cohort with over 1800 patients. Each patient on this cohort has actively consented to participate in research. This cohort has facilitated our robust feasibility assessment to establish that the time to target patient recruitment is attainable in the proposed timeline.

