### Intervention allocation

The experimental unit for this study will be a single patient episode (rather than the patient) identified by an event ID, since one patient can have two or more separate episodes of focal *status epilepticus* over the course of the study. Participant event/episode IDs will be randomly assigned to groups in a 1:1 ratio using block randomisation (6 blocks) by the sealed envelope software [26]. Based on the event ID the dedicated team member will be able to infer the study arm that determines the device setup for the first two days, i.e. active (early start) vs. sham (delayed start).

TDCS device marked as #1 will be set up individually for each experimental event for day 1 & 2 to either sham or active treatment with the aid of a special tool and instructional video. A second device marked as #2 will permanently be set up for active treatment and used for the remaining sessions (3 up to 14). One member of the team, not involved in the delivery of tDCS or data analysis, will be responsible for the randomization process, and sham/active device assignment and delivery. The random group assignment will be kept secret in a password protected file only accessible to the responsible team member. All remaining team members and all participants and relatives will be unaware to which treatment arm the participant is assigned. A record will be kept confirming when and by whom the randomisation code was requested and provided.

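### The different-focus rule alone does not protect the sham days of repeat episodes from earlier active tDCS

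*Protocol article*

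**What the plan says.** Recruitment aims for at least 30 episodes and allows fewer than 30 patients to supply them, "provided each event per participant has a different focal location". It adds: "If participants participate multiple times, they will be re-consented for each new focal event". It gives no interval since the last active session, and the Eligibility criteria do not mention earlier tDCS.

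Intervention allocation makes the episode the unit of randomisation: "The experimental unit for this study will be a single patient episode (rather than the patient) identified by an event ID". The reason it gives is that the same person may enter with more than one event. Randomization and intervention protocol agrees: "At baseline, participants will be randomly assigned to one of two arms for each focal event". Allocation is 1:1 in blocks, and the article mentions no stratum for first versus repeat episode.

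The early-start arm receives "20 min of active tDCS daily from the start of the intervention period (day 1) for up to 14 days". The delayed-start arm has sham on days 1 and 2, then up to 12 days of active stimulation. On mechanism, the Study rationale says that through long-term depression "a change in synaptic strength can be initiated that ultimately leads to structural long-term changes within the neuronal network", and that tDCS may lower connectivity in epileptic networks and spread beyond the epileptogenic zone.

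**The concern.** The sham-controlled part of each episode lasts two days, in about 15 delayed-start episodes. Its value rests on those days being untreated and blind. For a returning patient neither is secured by requiring a different focus.

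- **Carry-over.** If tDCS changes networks and not only the stimulated focus, as the rationale proposes, a new focus in the same brain may not be untreated.
- **Overlap.** Nothing stated prevents a second focus from being enrolled while the first is still under active treatment. A nominal sham day for one event could then coincide with an active session for another. This would matter however briefly the effect of tDCS lasts.
- **Blinding.** Sham current stops after the 15-second ramp, whereas active current runs for 20 minutes. Patients and carers who have been through full active sessions have something to compare with. The same people may complete the diary on which the primary endpoint rests, and the corroborating video and accelerometry are optional.

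Carry-over would tend to hide a true effect. Weakened blinding could push a diary-based outcome in favour of tDCS.

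**Working it through.** **Step 1: who has had active tDCS before re-entry.** An early-start episode gives active stimulation from day 1 and a delayed-start episode from day 3. The only returning patients without it are those whose earlier delayed-start episode ended, by resolution or withdrawal, during the two sham days. Nearly all others are pre-exposed, for up to 14 or up to 12 days.

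**Step 2: the plan's own figure.** Inputs from Target difference and sample size: 10% versus 30% responders, 5% type I error (taken as two-sided, since sidedness is not stated), 90% power, correlation 0.10, 14 observations per event.

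- Observations per arm, pooled formula without continuity correction: [1.960 × √(2 × 0.2 × 0.8) + 1.282 × √(0.1 × 0.9 + 0.3 × 0.7)]² / 0.2² ≈ 82.
- Design effect: 1 + (14 − 1) × 0.10 = 2.3.
- Events per arm: 82 × 2.3 / 14 = 13.5, so 14, and 28 in total. The stated 28 is reproduced.
- Power at 14 events per arm: 91.1%.

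**Step 3: illustration of dilution.** Two quantities are not in the documents and are assumed: f, the share of sham-arm episodes that are repeats, and c, the share of the 20-point effect carried into their sham observations. With the active rate held at 30%, the sham rate becomes 10% + 20 × f × c points and the gap becomes 20 × (1 − f × c) points.

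| f | c | Sham rate | Gap (points) | Power, 14 events per arm | Events for 90% power |
|---|---|---|---|---|---|
| 0 | any | 10% | 20 | 91.1% | 28 |
| 0.1 | 0.5 | 11% | 19 | 87.4% | 32 |
| 0.2 | 0.5 | 12% | 18 | 82.8% | 36 |
| 0.2 | 1 | 14% | 16 | 71.6% | 46 |
| 0.3 | 0.5 | 13% | 17 | 77.6% | 40 |
| 0.3 | 1 | 16% | 14 | 58.5% | 62 |

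With 14 sham events, f = 0.1 is between one and two events (14 × 0.1 = 1.4) and f = 0.3 is about four (4.2).

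**Step 4: limits of the illustration.** It inherits the plan's simplification that all 14 days contrast active with sham. It lets carry-over act only by raising the sham response rate. The endpoint, however, is a reduction of more than 50% from day 0. A residual effect already present on day 0 lowers the baseline and need not show as a further fall on sham days. It can also occur in repeat episodes of the early-start arm, where the calculation leaves the rate unchanged. The table shows sensitivity and is not an estimate.

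**The case against.** The different-focus condition is itself a safeguard, and it does not stand alone. The Intervention procedure section sets electrode positions separately for each event, with the cathode over that event's seizure site, and baseline is counted afresh on day 0. The mechanistic text is hedged, gives no duration, and says nothing about an effect on a later, different focus. A returning patient is by definition in a new episode despite earlier stimulation. The target could also be met by 30 patients with one episode each. All of this stands, and it limits the point to a risk.

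Three stronger readings are tempting and are not supported:

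- A reader might infer that sham days in repeat episodes do carry over treatment. No persistence is shown and no number of repeats is given.
- A reader might infer that repeat entrants will recognise sham. Both arms start with the same ramp, and the article says that published work supports the sham procedure. Weaker blinding is plausible but not demonstrated.
- A reader might count a chance imbalance of repeats between arms as bias. Under randomisation it is random error, reflected in the standard error, and repeat status is known beforehand and can be adjusted for.

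On overlap, the wording about separate episodes and new focal events suggests that none is intended, but it does not exclude it.

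Finally, this is a condensed article. The full protocol may set an interval, and a first-episode analysis would normally sit in the analysis plan. Its absence here is not the finding. The finding is that the article does state a re-entry condition, and that condition is too loose for the mechanism the article itself proposes.

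**Conclusion.** The point holds as a risk created by a stated rule. Re-entry and fresh randomisation, possibly to sham, are allowed on a different focus and renewed consent, although nearly all repeat entrants will have had active tDCS and the protocol posits long-term network effects. The rule alone excludes neither carry-over, nor overlap with active treatment, nor weaker blinding.

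The likely consequence of carry-over is a diluted contrast and lost power, not a false positive; only the blinding route could favour tDCS, and that route is unproven. The size cannot be derived from the documents. It is zero without repeats, and the losses in the table hold only under the assumed f and c. The matter is worth correcting because the sham contrast is short and the number of sham episodes small, so a few affected episodes would count.

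**What to change.** 1. In Recruitment, state that a new focus is not enrolled while the patient is still in the treatment period of an earlier study episode.
2. Include first versus repeat episode (prior study tDCS) as a covariate in the primary generalised estimating equation, or as a randomisation stratum if feasible. With about 30 events and possibly few repeats, a stratum may leave incomplete blocks, so the covariate is the simpler route.
3. Prespecify a comparison restricted to each patient's first episode as the check in patients naive to study tDCS. The covariate absorbs a difference in level between first and repeat episodes but does not undo dilution within repeats, so this comparison is needed as well. Repeat status is fixed before allocation, so the restriction keeps the comparison randomised.

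The article says that the analysis plan is finalised before unblinding, so items 2 (as a covariate) and 3 can still be placed there. The cost is one sentence, one model term, one extra analysis with fewer events, and possibly the loss of a few overlapping episodes.

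A minimum interval since the last active session is not required by this point. In a rare, acute condition it would cost episodes, and it would not remove an effect that is truly structural. Whether to set one is for the sponsor.
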